## Abstract

**Background:**

The impact of young drivers’ motor vehicle crashes (MVC) is substantial, with young drivers constituting only 14% of the US population, but contributing to 30% of all fatal and nonfatal injuries due to MVCs and 35% ($25 billion) of the all medical and lost productivity costs. The current best-practice policy approach, Graduated Driver Licensing (GDL) programs, are effective primarily by delaying licensure and restricting crash opportunity. There is a critical need for interventions that target families to complement GDL. Consequently, we will determine if a comprehensive parent-teen intervention, the Drivingly Program, reduces teens’ risk for a police-reported MVC in the first 12 months of licensure. Drivingly is based on strong preliminary data and targets multiple risk and protective factors by delivering intervention content to teens, and their parents, at the learner and early independent licensing phases.

**Methods:**

Eligible participants are aged 16-17.33 years of age, have a learner’s permit in Pennsylvania, have practiced no more than 10 h, and have at least one parent/caregiver supervising. Participants are recruited from the general community and through the Children’s Hospital of Philadelphia’s Recruitment Enhancement Core. Teen-parent dyads are randomized 1:1 to Drivingly or usual practice control group. Drivingly participants receive access to an online curriculum which has 16 lessons for parents and 13 for teens and an online logbook; website usage is tracked. Parents receive two, brief, psychoeducational sessions with a trained health coach and teens receive an on-road driving intervention and feedback session after 4.5 months in the study and access to DriverZed, the AAA Foundation’s online hazard training program. Teens complete surveys at baseline, 3 months post-baseline, at licensure, 3months post-licensure, 6 months post-licensure, and 12 months post-licensure. Parents complete surveys at baseline, 3 months post-baseline, and at teen licensure. The primary end-point is police-reported MVCs within the first 12 months of licensure; crash data are provided by the Pennsylvania Department of Transportation.

**Discussion:**

Most evaluations of teen driver safety programs have significant methodological limitations including lack of random assignment, insufficient statistical power, and reliance on self-reported MVCs instead of police reports. Results will identify pragmatic and sustainable solutions for MVC prevention in adolescence.

**Trial Registration:**

ClinicalTrials.gov # NCT03639753.

**Supplementary Information:**

The online version contains supplementary material available at 10.1186/s12889-023-16801-6.

## Background

The long-term goal of this research is to identify effective programs that can reduce adolescents’ risk for motor vehicle crashes (MVCs). The impact of teen and young adult MVCs is substantial, with young drivers constituting only 14% of the US population but contributing to 30% of all fatal and nonfatal injuries due to MVCs and 35% ($25 billion) of associated medical and lost productivity costs [1]. The current best-practice policy approach to teen driver MVC prevention, Graduated Driver Licensing (GDL) programs, have been effective largely by delaying licensure and restricting crash opportunity; they have not, however, directly led to increases in young drivers’ skills or competencies [2, 3]. In other words, GDL’s success has come from its focus on restricting *access* to high risk contexts and not on directly improving drivers’ *competence*. There is a critical unmet need for efficacious interventions that target young drivers’ inexperience directly to complement the structure put in place by GDL.

*Enhancing the Intermediate Period of GDL*: Most behavioural interventions directed toward newly licensed teens and their parents are intended to decrease novice drivers’ exposure to the driving environment, especially in conditions known to increase crash risk (e.g., driving at night, with friends) via codifying house rules or increasing parental surveillance using in-vehicle data recorders (IVDRs). Parent-teen agreements (or contracts) have demonstrated promising, but inconsistent effects on reducing teens’ risky driving behaviour and no effect on crashes [4–6]. Many interventions designed to increase parent limit-setting do not offer guidance to parents on best-practices related to parent-adolescent communication (e.g., active listening, respect for the teen’s autonomy), which can result in some parents rejecting the agreements as too business-like, while others embrace the clear contractual boundaries and push them (i.e., “my house my rules”) without soliciting input from their teen. This can diminish the opportunity for the teen to “buy-in” to the idea of limit-setting [7]. Similarly, IVDRs can provide parents with real-time or historical data about adolescents’ driving behaviours, which appears to be a promising strategy for encouraging safe driving [8] However, adolescents view IVDRs as intrusive, lessening their uptake in real-world settings [9, 10]. New solutions are needed that capitalize on the benefit of a strong mutually supportive parent-adolescent relationship, [11, 12] as well as recognize adolescents’ growing need for independence [13].

*Challenges Intervening with Parents and Teens to Promote Teen Driver Safety across GDL*: There continues to be a lack of effective behavioural interventions that directly target young drivers’ inexperience. Young drivers commonly exit the learner period still making considerable safety-relevant errors [14]. Emerging evidence suggests that parenting practices associated with transitioning teens to licensure are a reflection of both a continuation of parenting patterns from earlier developmental periods and anticipation of a new specific challenge salient to mid-adolescence [15]. However, there is very little longitudinal behavioural research on this topic [16]. Collectively, the limited body of research suggests that involved parent supervisors and an emotionally supportive supervisory experience can benefit teen drivers [11]; yet, there is still a strong degree of heterogeneity in how supervision is experienced by families, as well as a lack of experimental research mechanistically connecting parent-teen interactions during the learner phase to entry into the intermediate period of GDL and to safety outcomes. An expert panel convened by the National Highway Traffic Safety Administration (NHTSA) in 2012 concluded that: *“Greater parental involvement may help [reduce crashes] and should be an integral part of GDL and of the overall driver education* process. *Currently, there is no formal preparation for parents for this demanding role”.* [17].

*Need for comprehensive intervention*: The majority of intervention programs and basic research on parent-teen relationship factors concern *newly* licensed teens and their parents [5, 18]. Recently, success in improving specific driving skills (e.g., scanning for hazards) has been consistently demonstrated in applied laboratory settings, and there is emerging evidence to support a meaningful effect on safety as measured by reductions in crash risk [19–21]. Evaluations of driver training programs, primarily examining the contribution of training towards vehicle handling, and studies examining the quantity of practice (e.g., number of supervised practice hours) have both found inconsistent safety outcomes for teens [22–26]. Importantly, many prior evaluations of training programs directed to learner teens and parents have had methodological problems (e.g., lack of random assignment), and the programs themselves have been criticized for a lack of evidence base (e.g., poor correspondence to the task demands of independent driving) and poor engagement [27, 28].

In the current protocol, we evaluate a comprehensive parent-teen intervention, The Drivingly Program, which overcomes these issues. Drivingly is based on strong preliminary data and targets the family unit - as opposed to targeting parents and teens separately. This approach makes the best use of limited resources and is consistent with research indicating that a comprehensive intervention has the strongest potential to reduce MVCs [29].

## Methods

We propose a randomized controlled trial with 1,200 parent-teen dyads to evaluate our central hypothesis, which is that Drivingly can reduce adolescent drivers’ risk for a MVC during the first 12 months of licensure (Hypothesis 1). Our secondary focus is to evaluate Drivingly’s conceptual model (Hypothesis 2 and 3).

Hypothesis 2: Drivingly will:

improve practice driving (e.g. quantity, diversity, challenge).increase the frequency of parent-teen communication about traffic safety driving topics (e.g., GDL).increase adolescent drivers’ self-regulation (i.e., self-restriction of driving in conditions that are deemed more challenging and dangerous).increase parents’ limit-setting on post-license driving (e.g., passenger restrictions).reduce adolescents’ risky driving styles (e.g., angry, high-velocity) and increase safe driving styles (e.g., patient, cautious); and.

Hypothesis 3: Parent-teen (P-T) communication, practice driving, limit-setting, driving style, and self-regulation will mediate the effect of Drivingly on MVC risk.

### Description of Drivingly

The Drivingly Program is based on the Phase Transition Framework for reducing crash risk [30, 31]. It is a multicomponent crash prevention program combining effective interventions 32–35] into a comprehensive program targeting both parents and teens as they move through the licensure process. Drivingly, which spans the learner and junior license periods, consists of two semi-structured health coaching parent sessions, a web-based psychoeducational curriculum with a hazard anticipation and attention training component (e.g., Driver-ZED), and an on-road driver assessment (ODA) and feedback pathway for teen drivers. We review each of these components below.

*Parent-Sessions and Psychoeducational learning-to-drive Curriculum*: Parents receive two, brief, psychoeducational sessions with a trained health coach. The first parent session is an orientation to the program and the learner period, and the second parent session occurs while the teen is taking their ODA and is focused on readiness to drive and keeping teens safe after licensure. These sessions are delivered via a systematic health coach training process and training manual which includes a script to ensure consistency in the delivery of key messages. In complement to these sessions, parents and teens are supported with a web-based psychoeducational curriculum tailored to each stage of GDL and provided with sample conversation starters and activities to clarify goals and expectation for safe driving. The web-based psychoeducational curriculum contains 16 lessons for parents and 13 for teens, plus an online logbook. Structured using the Health Belief Model, 36] the curriculum entails an overview of risk factors for adolescents’ MVCs, the importance of the parental role as practice supervisor and risk-reducer, strategies for overcoming barriers to engagement, and reviews Pennsylvania’s GDL programme. The curriculum consists of two parts. Part 1 is aligned with the permit period and focuses on how to achieve high quality practice driving. There is also a complete practice driving curriculum based on the Drivingly **C**ommunicate **A**nticipate **R**egulate (CAR) Zone system. CAR scaffolds parents’ supervision by clearly defining driving zone specific targets for teens to practice in the domains of communication, anticipation and regulation (e.g., Communicate – Commercial Zone: Look and listen for other drivers and pedestrians trying to communicate with you). Part 2 is aligned with the restricted (or intermediate) license period and scaffolds parents’ involvement during the first year of licensure focusing on parental enforcement of GDL and planning for difficult social situations (e.g., impaired driving).

Prior to commencing the trial, a development phase was undertaken which consisted of four distinct components: (1) refinement of the scientific theory of change, which included the program theory of change (Fig. 1) and implementation plan; (2) content review and development for scalability (and pre-planning for sustainability), including development of online learning modules [https://drivingly.org/], finalization of a tailored on-road assessment and feedback pathway, and intervention administrator training manuals and processes; (3) mixed-method testing of website content for feasibility and acceptability with parents and teens (n = 13, [10 parents and 3 teens]), which included questionnaires on variables of interest from the open and closed-ended responses, as well as short interviews which were thematically analysed; and (4) expert review and feedback from driver educators concerning the on-road driver assessment and feedback methodology. Website feasibility and usability testing indicated high levels of both dimensions across parents, with lower levels among teens. Thematic analysis directed final changes to the web-based component of the program. Qualitative analysis resulted in three themes indicating ways the website could be improved. These included: Theme (1) More interactive activities for teens. Theme (2) More videos for parents and teens. Theme (3) Make information easier to consume on mobile devices. Driver educator feedback on the on-road assessment and feedback session was constructive, indicating feasibility and support. These changes were implemented prior to commencing the trial. A pilot test of a subset of these components (health coaching sessions and a paper version of the parent version of the psychoeducational curriculum) yielded evidence for improved parent-teen communication across a wide range of transportation safety topics [32].

**Fig. 1 Fig1:**
[figure not shown]
Drivingly Conceptual Model

*On-Road Driver Assessment and Feedback Pathway*: Teens receive an on-road driver assessment (ODA) administered by a certified driver instructor in a dual control vehicle in live traffic followed by an individualized feedback session among the instructor, parent and teen. The ODA exposes teens to challenges inherent in key driving environments (e.g., highway, rural areas, commercial roads) and is administered with minimal instruction and guidance by the evaluator, placing the teen fully “in the driver’s seat” mechanically and cognitively. In prior research, when deployed as an outcome assessment, the ODA has been shown to decrease risk for police-reported motor vehicle crashes by half [33]. It has been adapted into an intervention for the purpose of Drivingly. Although the ODA is an interventional component we collect the following data: the start and end time of the assessment, weather conditions, any changes to the route by the evaluator, participant or environmental factors (weather, traffic, road etc.), the number of driving hours the teen has, whether the teen is licensed already, the teen’s written feedback on how they think they performed, the evaluator’s constructive feedback to the teen, and brief notes on any critical driving errors made by the teen in each of the six driving zones (parking lot, residential zone, commercial zone, one and two-lane roadways, rural zone and highway zone). An in-vehicle recording device is used to record all drives; recordings are used for fidelity and quality assurance.

*Drivingly implementation Fidelity and Quality Assurance*: Fidelity checks and quality assurance (QA) will be completed for the first parent session and the ODAs. For the parent sessions, the study team administering the session will fill out a health coach fidelity checklist. Monthly review of the fidelity checklist and ensure that recordings of the parent session are stored on the study’s secure server. A second fidelity check on recorded parent sessions will be conducted by reviewing sampled videos along with the completed health coach fidelity checklist; feedback will be shared with health coaches to ensure minimal deviation from the health coaching manual. For the ODAs, the study team will complete monthly reviews of randomly selected video recordings of the assessment. These will be chosen from a list of all ODAs completed in the previous month with recorded parent sessions. Fidelity checks will be completed by reviewing the recordings of the ODAs along with the evaluation and feedback forms completed by the evaluator during the assessment. Notes of the fidelity checks will then be shared with evaluators to ensure adherence to the protocol. All paperwork completed by assessors and data entry into REDCap will be reviewed weekly by study team members.

### Participants

Eligible participants will include teenagers aged 16-17.33 years age at the time of enrolment, who will have their learner’s permit (Pennsylvania), intend to hold their permit for at least 6 months, have practiced no more than 10 h, and have access to the internet, a practice vehicle, and at least one parent/caregiver for each teen. Parents must be at least 18 years-old, have internet access, and be a licensed driver. Exclusion criteria include non-fluency in written or spoken English, having a sibling enrolled in the study, enrolled in other teen driving studies, and lack of internet and lack of a practice vehicle. Teens with self-reported or parent reported (of teen’s) visual, medical, or physical impairments that would require a handicap placard or assistive device to drive, or teens with pervasive developmental delays are ineligible to participate.

### Recruitment procedures

Participants will be recruited through a variety of strategies including mailings, emails, flyers, presentations in the community, databases for clinical trials (i.e., ResearchMatch ClinicalTrials.gov, etc.), schools and community organizations that give permission, word of mouth, social media postings and advertisements. We will work with the CHOP Recruitment Enhancement Core (REC) and the Pediatric Research Consortium (PeRC) using emails, letters, social media postings (CHOP’s Facebook or Instagram).

Interested people will contact the study team and be screened by phone for eligibility by a member of the study team. The study team will either schedule or re-contact interested participants for consent and assent. The study team will send parents an electronic copy of the consent (through REDCap) and schedule a zoom call with the parent and teen to verbally review the form; parents of participants will review and record written consent electronically in REDCap (via the e-Consent framework). With the REDCap-based e-Consent framework, signatures (typed name and electronic signature via mouse) will be obtained electronically. Parents will be asked to provide their child’s name and email. The REDCap e-consent framework is a secure, web-based, HIPAA-compliant, data collection platform with a user management system allowing project owners to grant and control varying levels of access to data collection instruments and data (e.g. read only, de-identified-only data views) for other users. Upon completion of the consent encounter, participants will be provided with their signed copy of the consent document by email, as well as the option to download a blank form for their records. Teens will then provide written assent via REDCap’s e-consent. In assent, participants will be asked to provide their signature, first and last name, date of birth, email, and the date that they are signing the form. After assent, participants will be emailed or able to download a copy of their signed form. If a participant turns 18 after enrolment, they will be re-consented again using the REDCap e-Consent framework. After dyads have documented parental consent, parental permission, and provided teen assent (baseline) and eligibility is confirmed, dyads will be randomized using a table of random numbers and start survey procedures.

### Compensation

Parent and teen participants will be compensated separately via study issued ClinCards. Teens in the control group will be compensated a total of $245 distributed across 6 surveys. They will receive $25 for completing the baseline survey, $20 for each of the 3 month post-baseline and post-licensure surveys, and $60 for each of the 3, 6, and 12 month post-licensure surveys. Teens in the intervention group will also receive $245 for completing all 6 surveys, as well as an additional $100 for completing the on-road driver assessment. Parent participants in both groups will be compensated a total of $65 for completing 3 surveys. They will receive $25 for the baseline survey and $20 for the 3 month post-baseline and post-licensure surveys.

### Study measurements

#### Crash

We will request crash records from the Pennsylvania (PA) Department of Transportation (DOT) for the teen participants enrolled in the study following previously validated procedures [33]. Crash reports will be requested for all licensed teen participants and sent to the study team via a secure FTP.

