### Statistical plan

With an initial sample size of 600 Drivingly dyads and 600 controls assuming 10% dropout in each group, a 1-year post-licensure crash risk in the unexposed group of 15%, and significance level (α) of 0.05, we will have 90% power to detect a hazard ratio (HR) of 0.59 for the first year of licensure. Alternatively, assuming a first-year control group crash rate of 20% the detectable HR is 0.65 for the first year of licensure; assuming a 25% first-year crash rate, the detectable HR is 0.69 [38]. Given our prior observed reduction of the ODA on crash risk of 53% (adjusted HR 0.47), these detectable HRs are conservative. Specifically, if the true HR is 0.47, we will have 99.4% power if the control group crash rate is 15%.

Risk ratios comparing the risk of any MVC involvement between Drivingly and Control will be estimated using modified Poisson regression [39]. Time-to-event (survival) analysis will be conducted to examine time to first MVC (from time of enrolment and from intermediate licensure) as the primary dependent variables of interest. We will create Kaplan-Meier curves to graphically depict the probability of these outcomes and compare the distributions of the two groups (Drivingly vs. Control) using the log-rank test. We will use a Cox proportional hazards (PH) model to estimate unadjusted hazard ratios, using an exact method for handling tied event times. To determine if there is effect modification by gender, we will use a PH model with a multiplicative interaction between gender and group (Drivingly vs. Control) and assess significance at the 0.10 level. We will report gender-specific hazard ratios between the Drivingly and Control groups because male drivers are at greater risk for MVCs than female drivers [40, 41].

To evaluate Drivingly’s conceptual model (Fig. 1) we will use marginal structural models with VanderWeele’s decomposition formulas for mediation analyses [42] This counterfactual approach to mediation analysis allows for the decomposition of total effects into direct and indirect components so we can estimate the proportion of the total effect of Drivingly on MVC risk mediated by each hypothesized process variable [42].

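### The Crash section names two populations for outcome data; under the licensed-teen wording, the time-to-crash analysis from enrolment is not a comparison of all randomised teens

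*Protocol article*

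**What the plan says.** Everything here is in the protocol article.

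- **Crash**, first sentence: "We will request crash records from the Pennsylvania (PA) Department of Transportation (DOT) for the teen participants enrolled in the study".
- **Crash**, next sentence: "Crash reports will be requested for all licensed teen participants and sent to the study team via a secure FTP".
- **Abstract, Methods**: "The primary end-point is police-reported MVCs within the first 12 months of licensure".
- **Statistical plan**: the survival analysis takes "time to first MVC (from time of enrolment and from intermediate licensure) as the primary dependent variables of interest".
- **Recruitment procedures**: once consent, assent and eligibility are in place, "dyads will be randomized using a table of random numbers and start survey procedures".
- **Participants**: at entry teens hold a learner's permit and intend to keep it for at least 6 months.
- **Description of Drivingly**: the second parent session, held while the teen takes the on-road assessment, is "focused on readiness to drive and keeping teens safe after licensure". The assessment ends with individual feedback to parent and teen. The Abstract places it after 4.5 months in the study.

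**The concern.** Randomisation takes place in the permit phase and licensure follows it. A request limited to licensed teens would therefore define the outcome data by something that happens after randomisation. That matters most for the analysis from enrolment, the one primary analysis whose clock starts near randomisation and which could compare the arms as randomised.

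Licensure could also differ by arm. Intervention families discuss readiness to drive and hear about critical driving errors before the intended 6-month permit period has ended; control families have usual practice. If some intervention teens postpone or forgo a licence, the licensed groups may no longer be alike. At stake is whether a lower crash risk among licensed teens can be read as safer driving, or partly as a different set of teens becoming licensed.

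**Working it through.** **1. Who has outcome data under each sentence**

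| Event | Enrolled-teen wording | Licensed-teen wording |
|---|---|---|
| Crash in the first year of licensure | observed | observed |
| Permit-phase crash, teen later licensed | observed | observed if the request reaches back before licensure |
| Any crash, teen never licensed | observed | not observed |

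The licensure-origin analysis needs only the first row. The enrolment-origin analysis needs all three. Under the licensed-teen wording, a never-licensed teen is either left out of it or event-free by construction.

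**2. The plan's own figures**

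The article gives no licensure share. Its nearest figure is the power statement: 600 per arm, 10% dropout, control risk 15% in the first year after licensure, and 90% power at HR 0.59.

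- Per arm: 600 × 0.9 = 540.
- Treated risk: 1 − 0.85^0.59 = 0.0914.
- Events: 540 × (0.15 + 0.0914) = 130.4.
- Schoenfeld: √130.4 / 2 × |ln 0.59| = 3.01. Power is 91.4% at one-sided 0.05 and 85.4% at two-sided 0.05.

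The article does not state sidedness; that is a separate matter. What counts here is that every teen who does not drop out is treated as followed through a post-licensure year, so the calculation says nothing about how many become licensed.

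**3. Size of possible selection in the licensure-origin comparison**

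Both settings assume no effect on any driver's risk and a control risk of r = 0.15. Licensure shares and the risk split are assumptions.

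*Setting A.* A share L0 = 0.85 of controls is licensed and a smaller share L1 of Drivingly teens. The additional unlicensed Drivingly teens would have had risk 2r.

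RR among licensed = [(L0·r − (L0 − L1)·2r) / L1] / r

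- L1 = 0.80: (0.1275 − 0.015) / 0.80 = 0.1406, and 0.1406 / 0.15 = 0.94.
- L1 = 0.75: (0.1275 − 0.030) / 0.75 = 0.1300, and 0.1300 / 0.15 = 0.87.

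*Setting B.* Half the teens have risk 20% and half 10%. In control, 90% of both halves are licensed; in Drivingly, 90% of the low-risk half and a smaller share of the high-risk half.

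- High-risk half 80% licensed: (0.5 × 0.8 × 0.20 + 0.5 × 0.9 × 0.10) / 0.85 = 0.125 / 0.85 = 0.147; RR 0.98.
- High-risk half 70% licensed: (0.070 + 0.045) / 0.80 = 0.144; RR 0.96.

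With L1 = L0 and no selection, RR = 1.

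These ratios come from the licensure-based end-point. They would be the same if records were requested for everyone.

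**4. The same settings over all randomised teens, unlicensed counted as crash-free**

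- Setting A: 0.1125 / 0.1275 = 0.88 and 0.0975 / 0.1275 = 0.76.
- Setting B: 0.125 / 0.135 = 0.93 and 0.115 / 0.135 = 0.85.

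These are also below 1, because fewer intervention teens drive. Agreement in direction between the two analyses therefore cannot separate safer driving from less driving. Licensure by arm can show which is in play.

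**The case against.** Five points can be made on the other side.

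- **The text never says that unlicensed teens are excluded.** A reader might infer that reports are requested for licensed teens only. The preceding sentence says enrolled teens, so the section is inconsistent rather than clearly restrictive. This stands.
- **Licensure is not a stated target.** A reader might infer that Drivingly aims to change who is licensed. Hypothesis 2 lists practice, communication, self-regulation, limit-setting and driving style, not licensure. The remark in the Abstract and Background about delaying licensure describes graduated licensing laws, which Drivingly is meant to complement. An effect on licensure is plausible, not documented.
- **The conditioning comes from the end-point, not the data request.** This stands. A wider request repairs the enrolment-origin analysis and leaves the licensure-origin one as it is.
- **An intention-to-treat result is not out of reach.** A reader might infer that none could be recovered. But a never-licensed teen cannot crash after licensure, so the all-randomised risk of being licensed and crashing within 12 months needs no records on unlicensed teens. Nor do the documents say that records could not be requested later. What would be lost is crashes by never-licensed teens, probably few.
- **An article condenses.** How never-licensed teens enter each model may be set out in the full protocol or analysis plan and is not held against the article. The conflict between two printed sentences, and between one of them and a named primary analysis, is not an omission of that kind.

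**Conclusion.** The point holds as an inconsistency with a practical consequence. The two sentences in the Crash section define different populations, and the licensed-teen sentence does not supply the data that the enrolment-origin analysis in the Statistical plan needs. If it is followed, that analysis is not a comparison of all randomised teens.

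The licensure-origin end-point carries a separate and smaller caution, since it conditions on a post-randomisation event. The null risk ratio of about 0.87 to 0.98 rests wholly on assumed licensure shares and assumed selection of higher-risk teens. It is modest beside the design hazard ratio of 0.59 and vanishes with equal licensure and no selection. It shows why licensure by arm should be reported; it does not show that the trial is biased.

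**What to change.** 1. Reword the Crash section so that both sentences name one population: crash records are requested for every randomised teen, from randomisation to the data cut, whether or not licensed.
2. Run the enrolment-origin time-to-first-crash analysis on all randomised teens.
3. Report the proportion licensed and the timing of licensure by arm beside the licensure-origin result, and interpret a lower crash risk in the light of any difference. Do not rely on the two analyses agreeing in direction, for the reason in step 4 of the working.

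The cost is a longer identifier list in a request already planned, plus a descriptive table. Never-licensed teens will probably add few events. Whether they can be linked must be confirmed with the Department of Transportation, because the article does not describe the linkage method. Enrolment was still open when the article was submitted, so the change was practicable then.
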